A time series analysis of Norwegian data from 1960 to 1995 found outlet density was significantly associated with violent crime [28]. A study set in Melbourne found that an increase in the number of outlets over a nine-year period was positively related to an increase in numbers of violent assaults recorded by the Police as taking place between 8pm and 6am (used as a proxy for alcohol-related assault for which specific data were not recorded) [29]. The fixed effects analyses, which controlled for spatial autocorrelation, modelled numbers of assaults and outlets rather than rates or density. This analysis further categorised postcodes into five clusters, based on socio-demographic factors, to investigate more detailed relationships and found the strongest associations in central and inner-city suburbs.

A study set in Los Angeles reported that a reduction in alcohol availability within census tracts (resulting from a riot in 1992) was associated with a significant reduction in gonococcal infection rates [32], partially mediated by neighbourhood social capital [33]. A significant reduction was also found for violent assaults [30] but a more sophisticated statistical analysis published one year later suggested that the association reported for violent assaults was no longer significant after using a different statistical modelling method [31]. The tenth study, using the same Californian dataset, found that changes in bar and off-premise outlet densities were positively related, and restaurant densities negatively related, to attempted and completed suicide rates [34].

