### Statistical analysis

The primary analysis will be for all alcohol outlets but we will also analyse the data using outlet densities for on- and off-sales separately where available. Our analysis plan has to take into account the nature of the data available through SAIL. Data on individuals nested within households nested within anonymised LSOAs will be available. Our analysis plan is:

(1) Full descriptive statistics.

(2) Spatial models to explore the relationship between counts/rates of the four outcome measures and outlet density. The models will account for the year and will adjust for aggregated population characteristics, such as the percentages of males and of certain socio-economic groups, and the median age. There are a number of methodologies that could be adapted to calculate spatial autocorrelation, including the Bayesian approach of Besag, York and Mollié [56], the random effects models developed by Gruenewald and colleagues and used in the three Californian longitudinal studies [25,26,34] and geographically weighted regression (GWR) models [57-60]. Moreover, more complex methodologies which take into account network distances – the distance to an outlet based on road and footpath measurements – can be adapted to explore these relationships. These methodologies include network distance calculations [61], the two-step floating catchment technique [62-64], and modified GWR models [65]. The different types of spatial models make different assumptions, model spatial autocorrelation differently and analyse the data in different ways; their relative merits will be explored as part of the study.

(3) A multilevel analysis using the hierarchy outlined above. We will use multilevel ordinal models of the defined categories of consumption for the WHS data and multilevel logistic models of the odds of hospital admission and A&E attendance as a function of change in individual outlet exposure, adjusting for confounding individual variables (age, gender, socio-economic status) and LSOA deprivation quintile. This method cannot be used for the crime data as we only know the location of offence with no information on individuals. Multilevel modelling is a well-established technique, see for example Goldstein 2003 [66], and we will fit models using the standard MLwiN [67] and R software [68].

In order to address the secondary research questions:

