(4) We will assess the impact on health inequalities by firstly stratifying the spatial and multilevel models using quintiles of the Welsh Index of Multiple Deprivation to examine whether the modelled associations vary with deprivation category. This method was used for postcode sectors in the Australian longitudinal analysis [29]. A further method which we will use is to model the interaction between LSOA deprivation score and change in outlet density and the two-way interaction including individual SES (using the NS-SEC) [69]. This method uses the whole dataset and the coefficients of the interaction terms give information on the effect on inequalities over time.

(5) Since the annual estimation of outlet density exposure automatically includes people who move residence, (from using the WDS within SAIL), our main models will correct for population migration. We will assess the impact of population migration by re-estimating annual outlet densities using the baseline population, repeating the models above, and comparing to the main models. Health selection bias can thus be assessed.

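### No committed model adjusts for urban-rural differences in outcome trend, although the walk and drive exposure measure depends on how built-up an address is

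*Protocol article*

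**What the plan says.** All references are to the Protocol article.

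- **Statistical analysis, item (3).** The multilevel models relate each outcome to change in individual exposure, "adjusting for confounding individual variables (age, gender, socio-economic status) and LSOA deprivation quintile". The list is given without any opening for further variables.
- **Statistical analysis, item (2).** The spatial models account for year and adjust for aggregated characteristics, "such as the percentages of males and of certain socio-economic groups, and the median age". This list is open, but it names nothing about settlement. Among the candidate methods is a model with locally varying slopes: "and geographically weighted regression (GWR) models [57-60". No candidate is chosen.
- **Statistical analysis, item (4).** Models are stratified by deprivation quintile "to examine whether the modelled associations vary with deprivation category", with the remark "This method was used for postcode sectors in the Australian longitudinal analysis [29". The plan will also "model the interaction between LSOA deprivation score and change in outlet density and the two-way interaction including individual SES".
- **Change in outlet density and alcohol-related harm.** Of that Australian study the article says "This analysis further categorised postcodes into five clusters, based on socio-demographic factors", and that it "found the strongest associations in central and inner-city suburbs".
- **Estimation of outlet density.** Exposure is built from network distances to outlets within a 10-minute walk and a 10-minute drive of each home.

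**The concern.** An exposure defined by what can be reached in ten minutes is tied to how built-up the address is. Change in that exposure may therefore differ between towns and countryside. Fixed urban-rural differences in the level of drinking, admissions or violence can cancel in an analysis of change. Different trends do not cancel, and a year term common to all areas does not remove them. Deprivation quintile is a different classification and cannot be relied on to separate urban from rural areas.

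If urban areas had both more exposure change and a steeper outcome trend over the study years, part of that trend gap would be credited to outlets. This bears on the primary question, which items (2) and (3) answer. The article itself reports that location within the city mattered in one earlier study, so area type was a foreseeable variable to hold constant.

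**Working it through.** **Inputs from the article**

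- 2.4 million adults and 1896 LSOAs: 2,400,000 / 1896 = 1266 adults per LSOA.
- About 13,000 alcohol-related admissions a year: 13,000 / 2,400,000 = 5.4 per 1000 a year.
- Planned contrast between extreme quintiles of change, 5.4 to 5.0 per 1000: 0.4 / 5.4 = 7.4%.

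**Assumed inputs (the article gives none of these)**

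- 35% of LSOAs are rural.
- Urban LSOAs have d = 0.5 or 1 SD more exposure change (within-class SD).
- The urban admission trend is steeper by g = 3%, 5% or 10%.
- Two periods of 2.5 years are compared, and the true outlet effect is zero.

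**Formulas**

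The urban indicator has variance k = 0.35 × 0.65 = 0.2275. Regressing the log rate ratio on standardised exposure change without a settlement term gives the expected spurious slope

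b = d × k × ln(1 + g) / √(1 + k d²).

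The mean of the top fifth of a normal distribution is 1.40 SD, so the extreme-quintile contrast is 2.8 × b.

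**Standard error**

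Expected admissions per LSOA and period: 1266 × 0.0054 × 2.5 = 17.1. The log rate ratio has SD about √(2 / 17.1) = 0.342, so the slope has standard error about 0.342 / √1896 = 0.0079. Simulation gave 0.0081, which is used below. Approximate rejection is Φ(z − 1.96) + Φ(−z − 1.96), with z = b / 0.0081.

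**Two cases in full**

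- d = 0.5, g = 5%: b = 0.5 × 0.2275 × 0.0488 / 1.028 = 0.0054; contrast 2.8 × 0.0054 = 1.5%; z = 0.67; rejection 10%.
- d = 1, g = 10%: b = 0.2275 × 0.0953 / 1.108 = 0.0196; contrast 2.8 × 0.0196 = 5.5%; z = 2.42; rejection 68%.

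**All cases, with simulation**

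Each scenario had 400 simulated datasets, all adjusted for deprivation quintile with robust standard errors. They were run once with weighted regression and once unweighted; both results are shown where they differ.

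| Urban excess in exposure change | Trend gap | Spurious contrast (formula) | Rejection (formula) | Rejection, simulated, no settlement term | Rejection, simulated, with rural indicator |
|---|---|---|---|---|---|
| 0.5 SD | 3% | 0.9% | 7% | 5%, 7% | 5%, 3% |
| 0.5 SD | 5% | 1.5% | 10% | 10% | 5%, 4% |
| 0.5 SD | 10% | 3.0% | 26% | 22%, 30% | 4% |
| 1 SD | 3% | 1.7% | 12% | 12%, 13% | 5%, 6% |
| 1 SD | 5% | 2.8% | 24% | 18%, 23% | 6%, 5% |
| 1 SD | 10% | 5.5% | 68% | 65%, 67% | 5%, 6% |

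**Cost in precision**

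Adding the indicator multiplies the standard error by √(1 + k d²), which is 1.03 at 0.5 SD and 1.11 at 1 SD. The simulated standard error went from 0.0081 to between 0.0083 and 0.0090, a rise of about 2% to 11%.

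**The case against.** The other side has real points.

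- **The plan is not blind to place.** Geographically weighted regression is a listed candidate, and its slopes and intercepts vary locally. The covariate list in item (2) is open. Under Presentation and mapping of the results, residuals of the multilevel models are to be mapped to find misspecification, including around clusters of outlets. A reader might infer that the plan fits a single outlet slope to all of Wales; the text does not support that. What remains is that the regression option is uncommitted and confined to item (2), and that the mapping is a diagnostic carried out after fitting. Neither commits any model to a settlement term.
- **Item (4) serves the inequalities question.** Deprivation is the apt stratifier there, and citing a study for stratified modelling does not oblige the plan to copy its strata. This stands, so the point belongs to items (2) and (3).
- **The Australian evidence is narrow.** It was set in Melbourne, concerned police-recorded night-time assaults, and modelled numbers of assaults and outlets. A reader might take it as proof of an urban-rural difference in admissions, A&E attendance or consumption. It is not; it only makes area type a variable worth considering.
- **The simulation is a simplification.** It is an ordinary regression with assumed inputs, without spatial terms or the other adjusters. It examines confounding, not a difference in the outlet effect between area types. This stands and limits the figures to an illustration of size.
- **The full analysis plan might add area type.** It might, but the article does state the adjustment set for the multilevel models, and settlement is not in it.

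**Conclusion.** The confounding point holds; the wider reading, that the outlet effect is forced to be equal everywhere, does not. No model to which the article commits itself holds urban-rural differences in trend constant, and the only prespecified effect modifiers are deprivation and socio-economic status.

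The size depends wholly on inputs that the article does not give. Over the range examined, the spurious contrast runs from about 1% to 5.5% against a planned 7.4%, and rejection under the null from about 5% to about 65%. With a 3% trend gap the effect is small: 0.9% to 1.7%, with rejection between 5% and 13%. It becomes material only when the gaps in exposure change and in trend are both sizeable. Nothing here shows that such gaps exist in Wales, or that the outlet effect is larger in urban areas. The case for acting is that the risk is foreseeable and the adjustment cheap. It is a change that should be made, held with medium confidence.

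**What to change.** Class each LSOA at 2005 as urban or rural from the population and mapping data already held, and fix the rule before outcome data are examined. Add settlement class and settlement-by-year to the models in items (2) and (3). The class is an LSOA attribute, so it can also be attached to the Welsh Health Survey and police data, which are linked only at that level.

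Report the outlet effect by settlement class as a secondary analysis, separate from the inequalities analysis in item (4), which can stay as it is.

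The cost is a few model terms and, for the two-class adjustment, standard errors about 2% to 11% larger. The cost of a finer classification, such as a separate town-centre class, or of the settlement-by-density interaction was not estimated.

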### Outlet density, neighbourhood deprivation and population migration

Two US papers investigated the association between outlet density and deprivation. Higher outlet densities were found in more deprived areas but paradoxically levels of consumption were highest in less deprived areas, suggesting that the mismatch between supply and demand could result in alcohol-related harm being disproportionately higher in people living in deprived neighbourhoods in proximity to alcohol outlets [35,36]. A cross-sectional study set in Glasgow, UK, found that the spatial association between outlet density and deprivation did not vary systematically, highlighting the importance of local context in the design of future studies [37]. Although it is clear from published research that selective population migration may account for a spurious widening of health inequalities over time [38,39], there are no studies which explicitly investigate this possibility for alcohol-related harm outcomes.

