### Primary research question

Overall, there is cross-sectional evidence from mainly American studies to suggest that higher outlet density is associated with alcohol-related harm, particularly involving violence. The evidence from longitudinal studies for associations between harm and a change in outlet density is less well established. Many methodological questions remain over the best way to measure outlet density and how to model the data. Little is known on the effect of a change in outlet density on inequalities in alcohol-related health and the role of population migration. Our primary research question for this study is:

What is the impact of a change in the density of alcohol outlets on alcohol consumption and alcohol-related harms to health in the community?

Our secondary research questions are:

1. Does a health selection effect from population migration at small-area level explain any observed associations between outlet density and alcohol-related harm?

2. What effect does change in outlet density have on population inequalities in alcohol-related health?

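### The deprivation-by-density interaction measures effect modification, which is only one ingredient of the effect on inequalities that secondary question 2 asks about

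*Protocol article*

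**What the plan says.** Under Primary research question, the protocol article asks as secondary question 2: "What effect does change in outlet density have on population inequalities in alcohol-related health".

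Item (4) of Statistical analysis gives two methods for it:

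- The spatial and multilevel models are stratified by quintile of the Welsh Index of Multiple Deprivation (WIMD), "to examine whether the modelled associations vary with deprivation category".
- The authors will "model the interaction between LSOA deprivation score and change in outlet density", and will also include individual socio-economic status (SES) in an interaction. The article comments that "the coefficients of the interaction terms give information on the effect on inequalities over time".

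The models behind item (4) are on two scales. The individual-level ones include "multilevel logistic models of the odds of hospital admission and A&E attendance as a function of change in individual outlet exposure". Consumption is modelled ordinally, and all of these models already carry the area's deprivation quintile as a covariate. The spatial ones relate "counts/rates of the four outcome measures and outlet density", and their link function is left open. Crime has only a spatial model.

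The background section on deprivation and migration gives location as a reason to study inequality. It reports for two US papers that "Higher outlet densities were found in more deprived areas". It also reports that a Glasgow study found no systematic variation of the association between density and deprivation.

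**The concern.** A difference in slopes between deprivation groups is effect modification. An effect on inequality is a change in the gap between groups, and it needs three things: the slope in each group, the density change each group experienced, and, for an absolute gap, each group's starting rate. Item (4) supplies only the first. Nothing elsewhere in the article combines slopes with the pattern of density change; the descriptive statistics and the mapping are not tied to question 2.

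The risk is one of interpretation. Results are meant for national and local policy makers. A near-zero interaction could be taken to mean that outlet change left inequality alone, although outlets had opened mainly in deprived areas and widened it.

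**Working it through.** **Inputs from the article.** 2.4 million adults, about 13,000 alcohol-related admissions a year, 1896 LSOAs, and a pilot range of five-year outlet change across local authorities of 5% to 46%.

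**The article's own figure.** 13,000 / 2,400,000 = 5.42 per 1000 a year, which agrees with the 5.4 used under Proposed sample size. No figure is given for the inequality question, so there is none to reproduce.

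**Assumptions.** Two deprivation groups (most deprived D, least deprived A) averaging 5.4 per 1000, with a baseline ratio of 2.00: 7.20 against 3.60, gap 3.60. Ratios of 1.5 and 3 are also tried. Odds ratios (OR) are per 10% rise in density. The 5% and 46% are borrowed from the pilot only as a span of plausible values. They describe outlet numbers in local authorities, not density in deprivation groups.

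**Formula.** With slope b and density change d in each group:

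- change in log-odds in a group = b × d
- change in the log odds ratio between groups = b_D × d_D − b_A × d_A
- interaction = b_D − b_A

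The density changes do not appear in the interaction.

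**Unequal change, common OR 1.05 (interaction exactly zero).**

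- D +46%, A +5%: rates become 8.995 and 3.689. The ratio goes from 2.00 to 2.44 and the gap from 3.60 to 5.31.
- D +5%, A +46%: rates become 7.376 and 4.502. The ratio falls to 1.64 and the gap to 2.88.
- Baseline ratio 1.5, first pattern: 1.50 to 1.83. Baseline ratio 3: 3.00 to 3.66.
- Smaller inputs, first pattern. At these low rates the ratio is multiplied by about OR^((d_D − d_A)/10). For OR 1.05 and the 41-point difference, 1.05^4.1 = 1.22. For OR 1.02, 1.02^4.1 = 1.085, giving about 2.17. For OR 1.05 and a 10-point difference, 1.05^1 = 1.05, giving about 2.10.

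**Equal change, common OR 1.05, both +20%.** The interaction is zero and the ratio stays at 2.00, but the gap goes from 3.60 to 3.97. Only the absolute scale moves.

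**Non-zero interaction, little or no change in inequality.**

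- OR 1.10 with +10% in D, OR 1.05 with about +20% in A: the ratio of ORs is 1.10/1.05 = 1.048, yet the ratio of rates stays at 2.00. This needs the larger slope to be matched by a smaller density change.
- Equal absolute rise of 0.3 per 1000 in both groups, both +20%: the gap stays at 3.60, the ratio falls to 1.92, and the ratio of ORs per 10% is 0.981.

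**Simulation.** 1000 runs per case; 379 LSOAs per extreme fifth (1896/5), 1266 adults each (2.4 million/1896), two years before and two after, SD of density change 15 percentage points. The two-sided 5% test of the interaction rejected in 4.9% of runs in the first unequal-change case, 5.2% in the equal-change case, and 99.7% in the offsetting case. The first figure is the test's nominal level, although the ratio had moved to 2.44.

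**The case against.** The strongest reply is that the article names no test, no null hypothesis and no rule for reading the coefficients. It says only that they give information, which is true. Question 2 can also be read as asking whether a given change in density harms deprived groups more, and stratification plus interaction answers that. A reader might infer that the plan tests for no effect on inequalities and will answer question 2 wrongly whatever the sample size. The text does not support that: it commits to no such conclusion.

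Other parts of the reply also stand:

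- Odds-ratio language fits the multilevel models only. In the spatial models the counterpart is usually a rate ratio.
- The equal-change case concerns the absolute scale alone. Choosing between scales is legitimate and is often left to an analysis plan.
- A non-zero interaction with unchanged relative inequality needs offsetting or near-zero density changes. The pilot's mean change was +6%, so near-zero net change everywhere is not the obvious expectation. With equal non-zero change in every group, a non-zero interaction does mean that relative inequality changed.
- The US evidence concerns outlet levels, not where outlets change, and the Glasgow study points the other way.

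What the reply does not remove is that item (4) is the only analysis offered for question 2, and that it never brings in the density change by deprivation group. The article expects local policies to produce both increases and decreases, so equal change across groups cannot be taken for granted.

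**Conclusion.** The point holds as a limit on what item (4) can show. Stratified associations and interactions measure effect modification on the model scale. If density change differs by deprivation, relative inequality can widen or narrow with a zero interaction; the absolute gap can move even when density change is equal. More data do not help, because the missing quantity is not in the coefficient.

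The size cannot be fixed from the article. The move from 2.00 to 2.44 (or to 1.64) rests on an assumed gradient, an assumed slope and borrowed density changes; milder inputs give about 2.10 to 2.17.

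It would be tempting to conclude that a significant interaction will often be false evidence of an inequality effect. On the relative scale this arises only under offsetting or near-zero changes, and the article gives no reason to expect those.

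This is a cheap improvement, not a flaw that invalidates the planned models.

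**What to change.** In item (4):

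1. Keep the stratified and interaction results, including those with individual SES, and label them effect modification.
2. Add, as the answer to question 2, a standardised contrast from the same fitted models. Predict each outcome by WIMD quintile at observed density, and again with density held at that study's own first year: 2005 for studies 1, 2 and 4, and 2009 for the A&E study, whose data run from 2009 to 2011. Use the spatial model for crime.
3. Report the change in the most-versus-least-deprived gap on the absolute scale (rate or risk difference) and the relative scale (ratio), with confidence intervals by delta method or bootstrap.
4. Tabulate the distribution of density change by quintile beside it.

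The cost is a change of wording and a modest post-estimation step. No new data or models are needed. The contrast takes the density effect as causal, which the plan's question about impact already does, and the report should say so.
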